## Abstract

**Background:**

Nursing home patients have complex mental and physical health problems, disabilities and social needs, combined with widespread prescription of psychotropic drugs. Preservation of their quality of life is an important goal. This can only be achieved within nursing homes that offer competent clinical conditions of treatment and care. *CO*mmunication, *S*ystematic assessment and treatment of pain, *M*edication review, *O*ccupational therapy, *S*afety (COSMOS) is an effectiveness-implementation hybrid trial that combines and implements organization of activities evidence-based interventions to improve staff competence and thereby the patients’ quality of life, mental health and safety. The aim of this paper is to describe the development, content and implementation process of the COSMOS trial.

**Methods/Design:**

COSMOS includes a 2-month pilot study with 128 participants distributed among nine Norwegian nursing homes, and a 4-month multicenter, cluster randomized effectiveness-implementation clinical hybrid trial with follow-up at month 9, including 571 patients from 67 nursing home units (one unit defined as one cluster). Clusters are randomized to COSMOS intervention or current best practice (control group). The intervention group will receive a 2-day education program including written guidelines, repeated theoretical and practical training (credited education of caregivers, physicians and nursing home managers), case discussions and role play. The 1-day midway evaluation, information and interviews of nursing staff and a telephone hotline all support the implementation process. Outcome measures include quality of life in late-stage dementia, neuropsychiatric symptoms, activities of daily living, pain, depression, sleep, medication, cost-utility analysis, hospital admission and mortality.

**Discussion:**

Despite complex medical and psychosocial challenges, nursing home patients are often treated by staff possessing low level skills, lacking education and in facilities with a high staff turnover. Implementation of a research-based multicomponent intervention may improve staff’s knowledge and competence and consequently the quality of life of nursing home patients in general and people with dementia in particular.

**Trial registration:**

ClinicalTrials.gov NCT02238652

## Background

The rapidly growing population of elderly persons in Europe is subject to frequent and numerous comorbidities, impaired organ function and problems linked to access to care and skilled treatment [1]. Dementia is increasingly common in the ageing population, with approximately 35 million affected people worldwide and 10 million in Europe [2, 3]. This number is expected to double within the next three decades, thus posing a considerable challenge for the healthcare system and society. Whereas one in four Americans die in a nursing home (NH) every year [4], almost half of the Norwegian citizens die in a NH [5]. In Norway, it has been estimated that 70,000 people have dementia, 34,000 of whom live in a NH [6] and have a stay of about 24 months mean length before death. More than 80 % of those living in a NH have dementia [7], often combined with stroke, heart failure or cancer. They have distressing mental health problems, such as agitation and depression [8], physical disabilities and unmet social requirements, and they are often in pain [9, 10]. The prescription of medication is high, including potentially harmful psychotropic drugs [11]. In addition, these people are in significant need of advance care planning [12] and meaningful activities [13].

In order to meet these challenges, the Norwegian Government encourages the municipalities to develop services and staff competence to improve mental health and quality of life (QoL) in NH patients and people with dementia as set out in the Coordination Reform (Norwegian Government report: 47 2008-2009). Objectives are in line with the National Research Program on Health, Care and Welfare Services 2015–2024 supporting research to develop and evaluate effective and complex interventions in large-scale research projects with a multidisciplinary approach, and including elderly NH patients with chronic diseases.

Responsibility for care and treatment of older people depends on the commitment and capability of the primary healthcare system. However, despite these complex tasks, NH patients are often treated by unqualified staff who lack education, knowledge and basic skills in terms of understanding patient behaviour, and who have insufficient expertise in how to treat and give proper care to persons with dementia [6].

### Rationale for the present trial

The number of cluster randomized clinical trials (RCT) including NH patients with and without dementia that are designed to investigate the efficacy of competence improvement programs combined with clinical treatment methods has increased in the last decade. For instance, implementation of introductory communication in the form of advance care planning (ACP) in NHs resulted in fewer deaths in hospitals and reduced resource use [12], better end-of-life care and pertinent ethical discussions, and satisfied relatives and staff [14]. Another example is the stepwise protocol of treating pain (SPTP) in people with dementia which succeeded in the reduction of agitation [15], mood syndrome [16] and pain [10]. Previously, systematic medication reviews, including staff education, workshops and face-to-face interaction between the prescribing physician and an expert-group, have been found to reduce unnecessary and harmful drug prescription [17]. Finally, a current systematic review by Testad et al. (2014) highlighted the benefit of systematic organization of activities [13] and described improvements in neuropsychiatric symptoms for reminiscence therapy [18–20], personalized pleasant activities [21–23] and person-centered care [24–26].

It is of key importance that these single interventions improved either behaviour such as agitation and aggression, reduced use of the total medication and antipsychotics, or hospital admissions. However, none of the single interventions resulted in an improvement of the QoL in NH patients. In addition, the evaluation of the actual implementation process of the interventions has largely been neglected.

### The COSMOS intervention

It is a basic requirement of human rights that a person is informed about her or his disease and be enabled to consider future plans and decisions [27–29], be out of pain [15, 30, 31], receive proper medical treatment [32, 33] and be involved in meaningful activities [13, 21, 34]. The COSMOS intervention is based upon results of earlier RCTs and will combine, implement and test the most effective components for developing an optimal multicomponent and systematic intervention by (Fig. 1):

**Fig. 1 Fig1:**
[figure not shown]
COSMOS components

*CO*mmunication*S*ystematic assessment and treatment of pain*M*edication reviewOrganization of activities and*S*afety

Changing clinical practice requires attention to multiple factors that influence individuals’ or groups’ willingness and ability to incorporate new knowledge of care [35]. Whereas education of clinicians alone is reported to be ineffective in changing care practices, complex multicomponent interventions that incorporate clinicians’ education have been reported to be successful [36]. The COSMOS trial is an evidence-based effectiveness-implementation hybrid trial funded by the Norwegian Research Council. We intend to use mixed qualitative and quantitative methods to test the effectiveness of the multifaceted intervention and to develop and test the implementation strategy for NH staff. In this paper, we describe the development of the COSMOS intervention; development of the education program; education of the COSMOS implementers (COSMOS ambassadors); implementation process in intervention NHs; support procedures, and statistical analyses.

The COSMOS program is based on evidence from the literature, and scientific and clinical experiences of the research group including research projects with cross-sectional, trajectory and RCT design, and a review of the literature. The COSMOS researchers are involved in education programs and teaching activities for healthcare professionals, people with dementia and relatives both at a national and international level. The combination of evidence for best practice and expertise related to education and training has been used to build up a systematic intervention which transfers evidence-based knowledge into an understandable everyday quality improvement intervention.

### Implementation strategies

One of the greatest challenges facing the global health community is to take proven interventions and implement them into the real world. The term “to implement” means “to carry out into effect”. Implementation research is defined as the related scientific investigation concerning the implementation process and the act of carrying an intention into effect in a real-world scenario [37, 38]. For the COSMOS trial, this means that research-based knowledge is to be transferred into practice with the selection of NH patients who mirror a broad variety of current quality in care and treatment offered in NHs.

A crucial aspect when assessing the effect of a complex intervention study is whether or not the intervention was implemented at all. Even when an intervention is superbly designed, real-world contextual factors may prevent the intervention from being realized as intended in a complex adaptive system [39, 40]. The intervention may not be completed, or it may be completed differently than originally intended, not systematic or plainly wrong. In other words, it is necessary not only to evaluate the intervention effect but also to evaluate implementation fidelity and sustainability [40].

### Aims of the COSMOS trial

The primary objective with the COSMOS trial is to improve the QoL in NH patients by enhanced communication in form of ACP, proactive assessment and treatment of pain, discontinuation of unnecessary medication and organization of activities. The secondary objective is to determine the effectiveness by core outcome measurements of mental and physical health, pain, sleep, safety, total drug use, hospital admission and cost-effectiveness. We also investigate how successful the implementation process was and staff satisfaction.

## Methods and design

This is a 4-month multicenter, cluster randomized and controlled effectiveness-implementation hybrid trial with follow-up at month 9, involving 571 participants from 67 NH units in Norway (Flow chart in Fig. 2). The mixed method design comprises the quantitative assessment with validated outcome measures and qualitative research of the intervention strategy by implementation indicators [40]. Very few studies have focused on these critical issues, hence the key attention of this project is to explore how the combination of an educational program for carers and research-based practice and competence may improve the QoL for NH patients. Until now, the efforts to improve standard of care in NHs have resulted in many “stints”; that is, most NHs may have had a campaign focusing on one of the single interventions. However, if a NH, for instance, offers optimal assessment and treatment of pain, this does not automatically mean that patients are also provided with meaningful activities.

**Fig. 2 Fig2:**
[figure not shown]
Flow chart of the COSMOS trial

### Settings and target population

Urban and rural NHs in Southern Norway will be included. The mix between urban/rural, big/small municipalities from different areas of Norway, extending over 700 kilometers apart, ensures a representative NH population. Systematic selection of the clusters will be achieved through established networks and information to related municipalities and NH managers. We strived to ensure collaboration from the top healthcare leaders of each municipality.

Inclusion criteria: NH patients with and without dementia, ≥65 years old, from 67 clusters, will be recruited. Diagnoses are based on patient’s medical records, medical examination and routine laboratory tests in the NH. The patients’ cognitive function is assessed by Mini-Mental State Examination (MMSE) [41] and Functional Assessment Staging (FAST) [42].

Exclusion criteria: Dying patients (life expectancy ≤6 months) or patients with diagnoses of schizophrenia will not be included.

### Research questions and study hypotheses in order to meet the aims of the study

To what extent will the implementation of ACP improve the decision processes and interactions between patients, staff and family and reduce hospital admissions and costs? We hypothesize that a systematic communication approach will empower patients and families to make preferred choices, be more independent and become better able to understand the complexity of current diagnoses, care and treatment.To what extent will previously unidentified pain be uncovered when the use of MOBID-2 is implemented? In patients with untreated pain, to what extent will a stepwise protocol of treating pain, show benefit on self-reported or proxy-rater assessed pain by MOBID-2 Pain Scale? We hypothesize that education and written material will result in improvements in pain assessment which will in turn result in excellent pain treatment and improved QoL.In patients with polypharmacy (≥4 drugs), to what extent will the systematic protocol of medication review based on face-to-face discussion between the responsible physician, NH staff and research team, following START and STOPP criteria [43] show benefits in terms of total medication use, use of psychotropic drugs and costs [44]. We hypothesize that a systematic medication review will reduce unnecessary medication and related costs, thereby improving the resources available.To what extent will a standardized and individual plan for activities increase activity time? We hypothesize that an individual plan for activities will improve the daytime activity provision to patients through regular follow-up and inclusion of relatives and volunteers.

### Cluster randomized effectiveness-implementation hybrid trial

Whereas pragmatic trials conduct a fixed intervention and do not try to control or ensure the delivery of services to meet realistic standards in normal practice settings, effectiveness-implementation hybrid trials also intervene and/or observe the implementation process as it actually occurs [37, 45]. Thereby, effectiveness-implementation hybrid designs are intended to assess the effectiveness of both an intervention and an implementation strategy. In this context, the expression “hybrid” signalizes a mixed method study design to cover the whole process of implementation and assessment of the intervention. Studies include elements of an effectiveness design (e.g. randomization to intervention and control group) and investigate, additionally, the implementation strategy by implementation outcome variables [45].

#### Cluster design and blinding

According to the research design, patients, units or even NHs are cluster randomized to care as usual or treatment. In a hybrid trial design, the implementation strategies, education and follow-up may be optimized during the process, for the purpose of gaining new understanding and insight. Because of this, the participants, patients and/or staff related to the clusters cannot be completely blinded regarding the group allocation. Meanwhile, the cluster randomized design is the most suitable design for implementation research, as it reduces the contamination between the intervention and control groups [46]. Furthermore, the cluster design takes into account the fact that the participants live together in the NH clusters.

#### Randomization

Using SPSS, each single NH unit is randomized to intervention or control condition per participating municipality and matched by urban and rural, prosperous and less well-to-do status and organizational conditions.

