### Data management and analyses

A data manager will be responsible for punching, validating and merging trial data. Data will be stored on approved servers at the University of Bergen (UoB). Demographic and clinical characteristics between intervention and control at baseline will be compared using Pearson *χ*^2^ test statistics for categorical variables and independent samples *t* test for normal variables (age, diagnoses and pain diagnoses). Analysis of covariance (ANCOVA) estimates the mean effect in each trial arm, weighted across clusters (1 cluster = 1 NH unit) according to number of patients within each cluster, and from this, the mean treatment effect is estimated at each time point [47]. The intraclass correlation coefficient (ICC) expresses the proportion of the total variance in data between included clusters. Primary efficacy population includes all patients with at least one post-baseline assessment (month 4 measure), and we will use a linear intercept mixed model in a two-way repeated measures configuration to assess change over time. Treatment effect will be expressed as estimated effect of intervention, along with a 95 % confidence interval and *p* values ≤0.05 for each time point. The Mann-Whitney *U* test will be used for non-normal distributed continuous variables such as QUALID [49], QUALIDEM [50], NPI-NH [52], CMAI [53], CSDD [54], MMSE [41], MOBID-2 Pain Scale [55], CGIC [59] and P-ADL [57]. Cost-utility analysis will be performed including costs for pharmaceuticals, resource use in NHs and use of external heath care facilities [44]. A full statistical analysis plan, including potential missing data imputation for each outcome measure, will be developed through the course of the study.

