### Sample size analyses

QoL is our primary outcome measure, and ongoing comparable intervention studies conduct similar sample size analyses; however, we are not aware of large-scale studies presenting the effect of a multicomponent intervention on QoL outcome measures such as QUALIDEM or DEMQOL. Based upon the magnitude of improvement in our previous RCT on pharmacological interventions [15] for neuropsychiatric symptoms in NH patients, we estimated that a 25 % reduction of the NPI-NH scale (SD 5 standardized effect size [SES] 0.4) for comparison of the intervention and control group at month 4. To measure a difference of this magnitude requires a minimum of 81 patients allocated to each arm of the trial, for a significance level of 5 % (two sided), a power of 80 % and equal allocation. As cluster designs lead to loss of power [47], the sample size should be multiplied by 1 + (*m* − 1)*ρ*, called the design effect, where *m* is the average cluster size and *ρ* = s2b/(s2b + s2w) is the ICC, where s2b is the variance between clusters, and s2w is the variance within clusters. Based on additional assumption of an estimated ICC of 0.157 in the earlier trial with an intervention over 8 weeks [15], an average of 10 eligible patients in each cluster gives a DE = [(1 + (11 − 1) × 0.157)] = 2.57 [15]. Thus, we need a minimum of 208 (2.57 × 81) patients per arm, or 416 patients in total. We expect a drop-out rate between 20 to 25 % [64] from baseline to month 4. Thus, we need a recruitment of an additional 104 participants (520 in total), with 32 clusters (NH units) in each arm. COSMOS will be conducted in at least 64 NH units (clusters), with an average of 8–12 patients on each unit.

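### Units are randomised within municipality and matched, but the ANCOVA and mixed model as described omit these factors; a unit-adjusted analysis without them is conservative to the extent that they predict outcome

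*Protocol article*

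**What the plan says.** The Randomization section restricts the allocation. Units are "randomized to intervention or control condition per participating municipality and matched by urban and rural, prosperous and less well-to-do status and organizational conditions".

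The section on data management and analyses describes three analyses of outcome:

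- An ANCOVA that "estimates the mean effect in each trial arm, weighted across clusters (1 cluster = 1 NH unit) according to number of patients within each cluster". No covariate is listed.
- For the primary efficacy population, "we will use a linear intercept mixed model in a two-way repeated measures configuration to assess change over time". I read two-way as arm by time. The level of the random intercept is not given.
- The Mann-Whitney U "test will be used for non-normal distributed continuous variables such as QUALID", followed by QUALIDEM and most of the secondary scales.

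Municipality, urban or rural setting, prosperity and organisational conditions appear in none of these. The section closes by deferring detail: "A full statistical analysis plan, including potential missing data imputation for each outcome measure, will be developed through the course of the study".

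The sample size section works "for a significance level of 5 % (two sided), a power of 80 % and equal allocation", with an ICC of 0.157, and takes no credit for the matching.

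**The concern.** Randomising within municipality and matching on further factors balances the arms on whatever those factors carry. The true sampling variance of the treatment effect then no longer contains the variation between municipalities or matched groups. An analysis that respects units but leaves the factors out still counts that variation as error. Its standard error is larger than the design warrants, its real type I error is below 5%, and part of the precision gained by the restricted allocation is not used.

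It is plausible that the factors matter here. The assumed ICC is large, the settings section describes urban and rural homes in big and small municipalities more than 700 km apart, and the investigators chose these factors for matching.

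**Working it through.** **The plan's own figure.** The article quantifies nothing about the matching. Its design effect reproduces as 1 + (11 − 1) × 0.157 = 2.57, and 81 × 2.57 = 208 per arm. The 81 itself does not follow from a standardised effect of 0.4 (about 99 per arm would be needed). That is a separate matter, and the ratios below do not depend on it. I use only the ICC, the two-sided 5% level and the 80% target power.

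**Inputs**

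- ICC: 0.157 (Sample size analyses).
- Patients per unit at baseline: 571/67 = 8.52 (Methods and design).
- Drop-out: 22.5%, the midpoint of the stated 20 to 25%. Analysed patients per unit: 8.52 × 0.775 = 6.6.
- Share f of between-unit variance explained by municipality and the matching factors: not given. Assumed range: 0%, 10%, 30%, 50%.

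**Step 1: variance of a unit mean** (total variance set to 1)

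v = 0.157 + (1 − 0.157)/6.6 = 0.157 + 0.128 = 0.285.

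**Step 2: ratio of standard errors, with the factors to without**

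r = √[(v − f × 0.157)/v]

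- f = 10%: √(0.269/0.285) = 0.972
- f = 30%: √(0.238/0.285) = 0.914
- f = 50%: √(0.206/0.285) = 0.851

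The reductions are about 3%, 9% and 15%. Equivalently, the unadjusted interval is 1/r times as wide: about 3%, 9% and 17% wider.

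**Step 3: actual type I error of the unadjusted test**

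Under restricted allocation the unadjusted test statistic has standard deviation r, not 1. Type I error = 2 × [1 − Φ(1.96/r)].

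**Step 4: power**

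Take the effect that gives 80% power at f = 0, so that effect/SE = 2.80.

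- Without the factors: Φ[(2.80 − 1.96)/r]
- With the factors: Φ(2.80/r − 1.96)

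| f | r | Type I error, unadjusted | Power without | Power with |
|---|---|---|---|---|
| 0% | 1 | 5.0% | 80% | 80% |
| 10% | 0.972 | 4.4% | 81% | 82% |
| 30% | 0.914 | 3.2% | 82% | 87% |
| 50% | 0.851 | 2.1% | 84% | 91% |

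Unadjusted power also rises with f, because the allocation has already reduced the true variance. The gain from adjustment is about 1.5, 4.4 and 7 points.

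**Step 5: simulation check**

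64 units were allocated within 4 to 32 strata, with 7 patients per unit, ICC 0.157, a standardised effect of 0.4 and 3000 runs per setting, using a unit-level t-test with and without stratum terms. Baseline power is higher here (about 85%), so the differences are what to compare.

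- f = 30%: power about 0.87 without and 0.90 with; mean interval width about 0.52 and 0.48.
- f = 60%: power about 0.90 without and 0.96 with; width about 0.51 and 0.43.
- f = 0 with 32 strata: power 0.851 without and 0.842 with, so adjustment costs about 1 point.

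**Step 6: the Mann-Whitney test**

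At patient level this test ignores units altogether. With 7 patients per unit, ICC 0.157 and no matching effect, its simulated type I error was about 14% at a nominal 5%.

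**The case against.** The strongest reply is that silence is not exclusion. The article lists no covariates at all, not even baseline score, and it promises a full analysis plan, where a covariate list normally belongs. That part stands: the factors are unmentioned rather than ruled out, and the unseen plan may include them. Against it, the article does describe the efficacy analyses in some detail. Run as described, they do not reflect the allocation described under Randomization.

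A reader might infer three stronger things that the document does not support.

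- *That every stated analysis gives intervals that are too wide.* A patient-level Mann-Whitney test errs in the opposite direction, and it is the test named for QUALID and QUALIDEM. A mixed model whose random intercept is not at unit level would also give intervals that are too narrow.
- *That power is certainly lost, or falls below the target.* The loss depends on f, which the article does not give. It is nil at f = 0, and on these assumptions unadjusted power does not fall below 80%, since the sample size took no credit for matching. Comparing adjusted power with a fixed 80% would overstate the gain.
- *That municipality alone stands for all the matching factors, at the price of a few degrees of freedom.* The article lists those factors separately from municipality and does not give the number of municipalities. Matched pairs among 67 units would use more than 30 degrees of freedom.

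**Conclusion.** The point holds as a conditional one. The design restricts allocation by municipality and matching factors, and the ANCOVA and mixed model as described do not use them. For an analysis that accounts for units, the omission makes the test conservative to a degree set by how well the factors predict outcome: modest at a 10% share of between-unit variance, material at 30 to 50%. The figures rest on the ICC that the sample size takes from an earlier trial, on about 6.6 analysed patients per unit, and on an assumed share. They say nothing about the Mann-Whitney analysis. The omission costs efficiency and does not bias the estimate; it is worth correcting because the remedy is cheap.

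**What to change.** In the analysis plan, specify the primary mixed model with a random intercept for nursing home unit and add municipality, the randomisation stratum, as a fixed effect. If units were matched in sets, use the matched set instead. Add any matching factor that varies within a municipality. Set a rule for merging strata whose units are all in one arm, and fix it before outcome data are analysed. That is a more workable point than unblinding, because the article says that patients and staff cannot be completely blinded.

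The cost is one or a few model terms and some between-unit degrees of freedom. How many depends on the number of municipalities or sets, which the article does not give. In the least favourable case simulated (32 strata with no predictive value), the price was about 1 point of power.
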